## Abstract

**Introduction:**

Many children in developing countries grow up in environments that lack stimulation, leading to deficiencies in early years of development. Several efficacy trials of early childhood care and education (ECCE) programmes have demonstrated potential to improve child development; evidence on whether these effects can be sustained once programmes are scaled is much more mixed. This study evaluates whether an ECCE programme shown to be effective in an efficacy trial maintains effectiveness when taken to scale by the Government of Ghana (GoG). The findings will provide critical evidence to the GoG on effectiveness of a programme it is investing in, as well as a blueprint for design and scale-up of ECCE programmes in other developing countries, which are expanding their investment in ECCE programmes.

**Methods and analysis:**

This study is a cluster randomised controlled trial, in which the order that districts receive the programme is randomised. A minimum sample of 3240 children and 360 schools will be recruited across 72 district school cohort pairs. The primary outcomes are (1) child cognitive and socioemotional development measured using the International Development and Early Learning Assessment tool, the Strengths and Difficulties Questionnaire, and tasks from the Harvard Laboratory for Development Studies; (2) child health (measured using height/weight for age, height-for-weight Z scores). Secondary outcomes include (1) maternal mental health, (using Kessler-10 and Warwick Edinburgh Mental Wellbeing Scale) and knowledge of ECCE practices; (2) teacher knowledge, motivation and teaching quality (measured with classroom observation); (3) parental investment (using the Family Care Index and Home Observation Measurement of the Environment and the Child–Parent Relationship Scale); (4) water, sanitation, and hygiene (WASH) practices; (5) acute malnutrition (using mid-upper arm circumference). We will estimate unadjusted and adjusted intent-to-treat effects.

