### Trial design

This study is an open-label CRCT, accommodating the phased and complete roll-out of the GES-LM Programme. The programme will be scaled to all of Northern Ghana’s 60 districts over 10 phases; each phase (equivalent to one school term) covering a district group (DG) of six districts, from September 2021 to September 2024 (figure 3A). Researchers at the the Institute for Fiscal Studies (IFS) randomised districts to DGs using R V.4.1.1. DGs will be enrolled into the evaluation study from January 2022 to September 2024 (hence, leaving out DG1) in six evaluation cohorts (ECs) (figure 3B). In each EC, one DG is allocated at random into the treatment group and one to the control DG. DG6 and DG7 are used first as control and later as treatment DGs, relying on different cohorts of children (those starting school in 2022 and those in 2023) (in different schools). DG10 will provide the control group for EC5 and EC6 using different schools. Control DGs will begin to receive the programme three terms after being enrolled into the study, after endline data collection has been completed (with the exception of EC6, where control will receive the programme after two terms). Baseline data collection will start at the end of January 2022 (after participant enrolment) (figure 3C). Data collection will proceed continuously through to the end of the project in early 2025. Figure 4 shows this design in a flow diagram, while figure 5 shows the participant timeline.

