### Sample size and sampling

Within each district, we plan to randomly sample five programme-eligible preschools (excluding efficacy trial schools) and eight children who are enrolled or about to enrol in the sampled preschool. In DG6, DG7 and DG10, we will sample children and schools twice (once for each cohort of children). When we sample for a second time, we will exclude schools previously enrolled into the study. This gives us a minimum total sample of 360 preschools and 2880 children and households.

Schools will be selected at random from a complete school list in each district provided by the GES. We will exclude focus on government schools, and exclude atypical schools, specifically only boys’ and only girls’ schools (more than 99% of government schools are mixed gender), as well as schools with less than 20 enrolled students. Doing so, we exclude 20 schools from the sampling frame (20 small ones, one of which has no boys enrolled in KG).

Our study participants will be children and their households, who attend or are due to attend KG. These will be identified from school enrolment lists, except for EC1 where due to the COVID-19 pandemic, school openings were different and lists were not readily available. We therefore sampled in this EC only from a census surrounding the school. To be eligible for the study, children must fulfil both of the following criteria (the same as in the efficacy trial):

Be aged between 3 and 5 years.Be enrolled or planning to enrol in the sample preschool in the coming term.

Where more than one child is eligible within a single household, we will randomly select one child to be a part of the study. Primary caregivers (PCGs) will be asked for their consent (and to give consent on behalf of their child) before being enrolled in the study. Model consent form and information sheet for PCGs are provided in online supplemental materials S2 and S3.

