### Sample size and power

As our design does not deviate in a substantive way from a conventional two-arm CRCT, we use standard CRCT methods to assess statistical power. For the power analysis, we consider the district as a cluster, providing us with 54 clusters. We consider the full sample size of 2,880 children (5 school per district-cohort, 8 children per school). We leverage data available from the efficacy trial to better inform how covariates increase our power to detect effects, including expected loss to follow-up, which we set at 6%.

We calculate minimum detectable effects (MDEs) using the following formula^28^:

(1)
$$MDE={\left(\frac{{\left(t_{\frac{\alpha }{2}}+t_{\beta }\right)}^{2}\sigma^{2}(m\rho \left(1-R_{c}^{2}\right)+\left(1-\rho \right)\left(1-R_{p}^{2}\right)}{n}\right)}^{\frac{1}{2}}$$

α denotes the significance level, β power, ρ unconditional intracluster correlation (ICC), *t* is the critical value of the t-distribution, σ is the SD of the outcome, *n* is children per arm, *m* is children per cluster, $R_{c}^{2}$ is proportion of cluster-level variance component explained by covariates and $R_{p}^{2}$ is the individual equivalent. One can interpret the effect of $R_{c}^{2}$ and $R_{p}^{2}$ as altering the ‘variance inflation factor’ of the power calculation—when they equal zero, the formula reduces to the standard CRCT one. We set α to 0.05, β to 0.8.

We estimate the ICC for each outcome data using data from the efficacy trial (ranging from 0.011 to 0.110). Note that we cannot conduct the same exercise for all of our primary outcomes, as some were not included in the original trial. The MDEs for some of our primary and secondary outcomes measured at the child/household level are shown in table 1. The power to detect effects at the school level is significantly more limited.

**Table 1 T1:** Minimum detectable effects (MDEs)

Outcome	MDE
Cognition factor score	0.110
Middle upper arm circumference	0.137
Knowledge Infant Development Index	0.119
Family Care Index	0.210
Parent–child interaction (Child–Parent Relationship Scale)	0.126

Each outcome controls for its baseline value only.

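### The abstract sets the minimum sample at 3240 children; the sampling and power sections set it at 2880 for the same 360 schools

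*Protocol article*

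**What the plan says.** Three places in the protocol article give the number of children.

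- **Abstract, Methods and analysis:** "A minimum sample of 3240 children and 360 schools will be recruited across 72 district school cohort pairs".
- **Sample size and sampling:** "This gives us a minimum total sample of 360 preschools and 2880 children and households". This total follows a sampling rule of five schools in each district ("Within each district, we plan to randomly sample five programme-eligible preschools (excluding efficacy trial schools") and, in each school, "eight children who are enrolled or about to enrol in the sampled preschool".
- **Sample size and power:** "We consider the full sample size of 2,880 children (5 school per district-cohort, 8 children per school". Loss to follow-up of 6% is a separate input to the power calculation.

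The number of district-cohorts comes from two further statements. Trial design describes "each phase (equivalent to one school term) covering a district group (DG) of six districts" and six evaluation cohorts, each with one treatment and one control group. Sample size and sampling adds: "In DG6, DG7 and DG10, we will sample children and schools twice (once for each cohort of children".

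**The concern.** The abstract and the sampling section both call their figure a minimum, and both refer to the same 360 schools, yet the child counts differ. They cannot both be the product of one sampling rule: one implies eight children per school and the other nine.

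The planned sample size is a headline commitment, and readers of the results paper will compare achieved recruitment with it. If the field team applies the sampling rule and recruits exactly eight children in every school, the trial meets the minimum in the body of the article and falls 360 short of the minimum in the abstract. If nine per school was the intention, the sampling section gives the wrong instruction, and Table 1 describes a different sample from the one to be recruited.

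**Working it through.** **Inputs**

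| Quantity | Value | Where stated |
|---|---|---|
| Evaluation cohorts | 6 | Trial design |
| District groups per cohort | 2 (one treatment, one control) | Trial design |
| Districts per group | 6 | Trial design |
| District groups in the study | 9 (10 less DG1) | Trial design |
| Groups sampled twice | 3 (DG6, DG7, DG10) | Sample size and sampling |
| Schools per district | 5 | Sample size and sampling |
| Children per school | 8 | Sample size and sampling; Sample size and power |
| Clusters for power | 54 districts | Sample size and power |
| Loss to follow-up | 6% | Sample size and power |
| Intracluster correlation (ICC) | 0.011 to 0.110 | Sample size and power |

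**Step 1: reproduce the design counts**

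- District-cohorts: 6 × 2 × 6 = 72. Cross-check: (9 + 3) × 6 = 72. This matches the abstract.
- Schools: 72 × 5 = 360. This matches the abstract and the sampling section.
- Children: 360 × 8 = 2880. This matches the sampling and power sections, but not the abstract.

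**Step 2: look for a route to 3240**

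- Children per school: 3240 / 360 = 9 exactly.
- Inflation for 6% loss: 2880 / 0.94 = 3064 (rounded up), or 2880 × 1.06 = 3053 (rounded up). Neither is 3240.
- Loss needed to bridge the figures: 1 − 2880 / 3240 = 11.1%. The article does not state such a loss.
- Children versus households: the sampling section takes one child per household and gives 2880 for both, so this does not explain the gap.

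**Step 3: size of the gap**

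3240 − 2880 = 360 children; 360 / 2880 = 12.5%; 360 / 3240 = 11.1%.

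**Step 4: effect on the minimum detectable effect (MDE)**

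The article does not give the covariate R² values, so this is an illustration and does not reproduce Table 1. Assumptions: both R² terms 0, SD 1, 54 equal clusters, no loss, t quantiles on 52 degrees of freedom (2.007 + 0.849 = 2.855; squared, 8.152).

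Equation (1) as printed then becomes MDE = √[8.152 × (mρ + 1 − ρ) / n], with n children per arm and m per cluster. The usual two-arm comparison has an extra factor of 2 inside the root, which the printed equation lacks, so both versions are shown.

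- Eight per school: n = 2880 / 2 = 1440; m = 2880 / 54 = 53.33.
- Nine per school: n = 3240 / 2 = 1620; m = 3240 / 54 = 60.
- Variance term at ICC 0.011: 53.33 × 0.011 + 0.989 = 1.576 (eight); 60 × 0.011 + 0.989 = 1.649 (nine).
- Variance term at ICC 0.110: 53.33 × 0.110 + 0.890 = 6.757 (eight); 60 × 0.110 + 0.890 = 7.490 (nine).

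| ICC | Version | 2880 children | 3240 children |
|---|---|---|---|
| 0.011 | as printed | 0.094 | 0.091 |
| 0.011 | with factor 2 | 0.134 | 0.129 |
| 0.110 | as printed | 0.196 | 0.194 |
| 0.110 | with factor 2 | 0.277 | 0.275 |

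With normal quantiles and 6% loss, the equation as printed gives 0.0945 and 0.0911 at ICC 0.011, and 0.193 and 0.191 at ICC 0.110. The relative change is about 3.6% at the lower ICC and about 0.8% at the higher one under either set of assumptions.

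**The case against.** The strongest reply is that the operative text is consistent. The sampling rule, the total derived from it and the power calculation all say eight per school and 2880. Field staff sample from the rule and not from the abstract, so the outlier is one number in a summary. Power was also calculated on the smaller figure, so recruiting 3240 would make Table 1 slightly pessimistic, not optimistic. Finally, the article does not make the total a success criterion, and a trial that exceeds 2880 still satisfies the sampling section.

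Much of this stands. The sampling rule itself is clear, the inferential effect is negligible, and a shortfall against the abstract arises only if recruitment stops below 3240. The use of the total as a yardstick for completed recruitment is a judgement about how readers treat it, not a rule in the article. None of this explains 3240, however. The two figures are not enrolled versus analysed, since both are stated as minimums for the same schools and the power section treats loss separately. A sample size stated in the abstract is a figure that readers rely on, and this one does not follow from the design.

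**Conclusion.** The contradiction is real. The article's own inputs give 2880 children; 3240 needs nine children per school, which is stated nowhere. The gap is 360 children (12.5% of 2880). This conclusion rests only on counts in the article and needs no outside assumption.

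The consequence is an inconsistent recruitment commitment. It does not alter the power conclusion: over the stated ICC range the MDE changes by less than 4%. That percentage depends on the assumptions of no covariate adjustment and 54 equal clusters, and the absolute MDE levels depend further on whether the factor of 2 is included. The correction should be made, but it is a matter of consistency and not a design flaw.

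**What to change.** State one minimum throughout.

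- **If eight children per school is intended**, as the sampling and power sections say, change 3240 to 2880 in the abstract. This is a one-number edit with no effect on design, budget or analysis.
- **If nine per school is intended**, change eight to nine in the section on sample size and sampling, change 2880 to 3240 there and in the section on sample size and power, and recalculate Table 1. The cost is a rerun of the power calculation and fieldwork for 360 more children than the present sampling rule provides.

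Any other public statement of the planned sample should carry the same figure.

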**Ethics and dissemination:**

Study protocols have been approved by ethics boards at the University College London (21361/001), Yale University (2000031549) and Ghanaian Health Service Ethics Review Committee (028/09/21). Results will be made available to participating communities, funders, the wider public and other researchers through peer-reviewed journals, conference presentations, social and print media and various community/stakeholder engagement activities.

**Trial registration number:**

ISRCTN15360698, AEARCTR-0008500.

STRENGTHS AND LIMITATIONS OF THIS STUDYThis trial assesses the effect of a programme previously demonstrated to be effective in a small efficacy trial now adopted by government and being brought to scale.Scaling up effective interventions has proven challenging in the past; this study will provide much needed evidence on whether an intervention designed to be scalable can be effective.A challenge in this study is measuring and adjusting for differences in programme delivery quality across different districts.

## Introduction

Over 250 million children worldwide under the age of 5 years are at risk of not achieving their developmental potential due to poverty, poor health and nutrition, and deficient care and stimulation.^1^ The majority of these children live in low/middle-income countries (LMICs), 1.6 million in Ghana.^2^ In Northern Ghana, the setting of this study, and where most families live on less than US$2 per day, 20% of children under 5 years are stunted and 39% of children 3–4 years old are off-track cognitively.^3^

School enrolment alone does not offset these disadvantages: in spite of great global progress in primary school enrolment, around 125 million children lack age-appropriate skills around the world.^4^ Years of exposure to poor environments have adverse long-run effects on children’s cognitive and socioemotional development, health and psychological well-being, and earning potential, increasing the risk of poverty, early marriage and parenthood.^5^ A recent Lancet review highlights that ‘children at elevated risk for compromised development due to stunting and poverty are likely to forgo about a quarter of average adult income per year’.^6^

As shown in a substantial body of evidence and increasingly recognised by policymakers, early childhood care and education (ECCE) interventions offer an opportunity to ameliorate these detrimental effects at a time of heightened developmental sensitivity and malleability.^7^ The Government of Ghana (GoG) has implemented some of the most advanced ECCE policies in the sub-Saharan Africa (National Early Childhood Care and Development Policy in 2004 and 2 years of public pre-primary education in 2007), resulting in universal net enrolment.^8^ The GoG, however, recognises that significant challenges remain: one-third of Ghanaian preschool (kindergarten (KG)) children lack the necessary skills to thrive in school, including early academic and behavioural skills, socioemotional development and aspects of physical health including motor development,^9^ and deficits persist and grow through primary school, where one-fourth of pupils do not meet all proficiency cut-offs.^10^

In 2017/2018, [name] and SK led an efficacy trial of Lively Minds—a holistic ECCE programme which engages parents and preschools to achieve healthy child development of children 3–5 years old in rural Ghana and promotes inclusion of children with disabilities. The trial revealed a positive impact on child health, as well as cognitive and socioemotional development, partly mediated by improvements in parenting practices.^11^

As a result of this evidence, the Ghana Education Service (GES) plans to integrate the Lively Minds Programme with core instruction across all preschools in Northern Ghana over the next 4 years aiming to cover over 4000 preschools, reaching 1.3 million children, reducing costs to $7 per child per year (less than one-third of the original cost, and significantly below typical group parenting programme costs in LMICs, estimated to be US$30–US$35 per child).^12^ Ownership of the programme has been transferred from the non-governmental organisation (NGO) that developed it to GES. We will therefore refer to the programme as the GES Lively Minds (GES-LM) Programme.

This study is a cluster randomised controlled trial (CRCT) evaluating this scale-up, with randomisation achieved through randomisation of the order in which districts begin to receive the programme. We will assess whether the impacts found at efficacy trial stage are sustained and investigate key mechanisms underlying these in order to determine how implementation and cost-effectiveness could be further improved.

### Objectives

The project’s key research questions are as follows:

What is the impact of the GES-LM at scale on child development?How does the impact of the intervention vary by child, teacher, classroom/school and district characteristics?What role do intervention fidelity and compliance play (intensity of training, dosage, hygiene promotion, quality of play sessions, supervision by teachers and district education offices) and how can the design be adapted to maximise cost-effectiveness?Are impacts achieved through changes within the classroom/school and/or the children’s home environments, including teacher and parent behaviour?

## Methods and analysis

### Study setting

The programme will be rolled out at scale in Northern Ghana, where prevalence of chronic malnutrition is nearly twice as high as the national average (at 33% and 19%, respectively) and 60%–70% of the population were classified as poor in 2017, compared with 23% nationally.^13 14^ Baseline conditions among the sample in the efficacy trial reveal that one-third of children (3–5 years) had acute malnutrition and had experienced diarrhoea in the last 30 days; less than one-third could identify a shape such as a triangle and even fewer were able to sort figures based on colour and shape. Around half of the mothers were at risk of depression and only 13% reported that *anyone* in the household had played with the target child in the last 3 days. The children live in households of on average 10 members in which only 20% ever attended school and even fewer are literate (8%). Household sanitary infrastructure is largely lacking—nearly 80% report that they defecate openly. Access to public infrastructure is dismal: one in three communities do not have access to electricity and more than half cannot be accessed for 1–2 months of the year due to lack of paved roads.^15^

### Intervention description

The programme developed by the NGO Lively Minds aims to provide preschool age children with the foundations they need to succeed in school. As young children transition to school, they draw on multiple skills to succeed in the classroom, including early academic and behavioural skills, socioemotional development and aspects of physical health including motor development.^16 17^ Exposure to quality ECCE has the potential to improve school readiness across these various domains. Current conceptualisations of ECCE quality rest however not only on children’s experiences in their classroom, but also on their home environments, and point to the critical role that warm, nurturing, responsive and stimulating relationships with caregivers both at home and school play. Attachment theory focuses on the importance of consistent and sensitive interactions with teachers and parents^18^; constructivist learning theories focus on the development of cognitive skills through engaging in age-appropriate activities.^19^ Further, regular communication between parents and schools allows them to work together toward children’s learning and development and has been shown to improve longer‐term academic outcomes for preschool and KG children.^20 21^

Building on this theoretical framework, the Lively Minds intervention has four core aims:

To increase children’s opportunities for scaffolded, individualised or small group learning experiences at home and at preschool.To reduce harsh and corporal punishment while improving positive behaviour management ensuring that children receive responsive, warm, nurturing caregiving from their caregivers at preschool and at home.To improve hygiene practices and nutritional content in order to improve children’s physical health while considering constraints parents face.To strengthen engagement of mothers with children’s schools in order to facilitate a more holistic approach to children’s care and learning, as well as empower mothers to have a say in the quality of education their children receive at school.

To this end, the intervention consists of three key components:

Play schemes (PS) for children attending KG (age 3–5 years): children learn through play rotating between five play stations set up in KG classrooms, each of which is run by a trained woman from the community (often the mother of one of the children participating). At each play station, mothers teach a small group of children (no more than 5) using discovery-based teaching methods through simple games and activities such as puzzles, sorting by shape and size, recognising letters and numbers, reading books and building with blocks. Children who are not in one of the five groups play outdoor games led by one of the trained women while they wait for their turn. Children have to wash their hands with soap before participating in the PS so that they become sensitised to the importance of this practice.Parenting courses for the women who run the PS: monthly parenting workshops which aim to increase awareness and understanding of the sensitive caregiving and stimulation that children need to thrive, the adverse effects of harsh punishment and reinforce behaviours encouraged by the programme including practices that stimulate children’s development and health.Training and supervision of KG teachers: KG teachers are the *trainers* within this programme. They enrol mothers in the community to volunteer to implement the PS, train the mothers on how to do this, oversee implementation of the PS in their classrooms and lead the parenting workshops. In order to do this, KG teachers receive ongoing training in all aspects of the programme and supervision visits from the central programme team, situated within the Ghana Ministry of Education.

Figure 1 summarises the conceptual framework underpinning this programme, highlighting key channels through which the programme is expected to impact children’s developmental outcomes and school readiness. A critical and distinguishing feature of the programme is that through engaging KG teachers and mothers, it has the potential to *simultaneously* improve the home and preschool environments; typically, ECCE programmes are designed to target one or the other.

